#### Statistical Design, Power, and Analysis Plan

Sample size calculations and pre-determined statistical power for this randomized, double-blind, placebo-controlled, parallel group design clinical trial are based on the primary outcome, casual SBP. Sample size and power were estimated based on preliminary data from our crossover design pilot trial on nicotinamide riboside supplementation in midlife and older adults (22). In subjects from our pilot trial who had initial above-normal SBP, the change from baseline in SBP with nicotinamide riboside supplementation was –12.8 mmHg (i.e., SBP decreased) and –4.2 mmHg with placebo treatment, resulting in a difference of 8.6 mmHg between treatment arms. The standard deviation of change was estimated as 11.6 mmHg for the nicotinamide riboside condition and 13.5 mmHg for the placebo condition. This yielded an estimated effect size of 0.68, which was used to determine the required sample size for the current protocol. It was determined that 47 subjects per group (94 total) would be required to achieve a power of 90% with a two-sided significance level of α = 0.05. To account for a potential drop-out rate of 20%, i.e., the rate observed in our pilot study, a total of 118 participants will be enrolled and equally randomized to an intervention group, with 59 participants/group.

Descriptive statistics will be provided for all baseline and outcome variables. Means and standard deviations will be calculated for all continuous variables, proportions will be calculated for categorical or ordinal variables, and 95% confidence intervals will be provided when appropriate. We will use the *t*-test to compare the change in outcome measures between nicotinamide riboside and placebo treatment groups because all outcome variables are continuous. All outcome variables will be assessed and confirmed for normality and data transformations will be performed, if necessary, prior to performing comparisons. All comparisons will be made on intention to treat principle and conclusions will be made using a two-sided significance level of α = 0.05. Furthermore, linear regression will be used to adjust for potential confounders such as age, baseline BP, and use of antihypertensive medications. We are aware that statistical significance does not imply clinical significance; thus, we will make clinical interpretations carefully.

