#### Randomization and Blinding

After baseline assessments, participants will be randomized to 3 months of nicotinamide riboside or placebo supplementation. Block randomization will be employed based on age (50–64 years vs. ≥ 65 years), sex (male vs. female), and SBP (elevated BP/stage 1 hypertension: 120–139 mmHg vs. stage II hypertension: 140–159 mmHg). Randomization will be performed by a staff research assistant who is not involved with data acquisition or analysis and will remain unblinded for the duration of the study. The Microsoft Excel random number generator function will be used to assign participants to nicotinamide riboside or placebo treatment. Investigators responsible for collection and analysis of outcome measurements will be blinded to participant group assignment. Participants also will be blinded to their treatment group.

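### The powered primary comparison is an unadjusted t-test on change: valid, but less precise than a pre-specified ANCOVA on baseline SBP and the randomisation factors

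*Protocol article*

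**What the plan says.** Under Statistical Design, Power, and Analysis Plan, the sample size and power "are based on the primary outcome, casual SBP". The same section uses a t-test "to compare the change in outcome measures between nicotinamide riboside and placebo treatment groups" for all outcomes, and "conclusions will be made using a two-sided significance level of α = 0.05". The only reason given for the t-test is that the outcomes are continuous, which would justify a regression equally well. The section then adds that "linear regression will be used to adjust for potential confounders such as age, baseline BP, and use of antihypertensive medications".

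Under Randomization and Blinding: "Block randomization will be employed based on age (50–64 years vs. ≥ 65 years), sex (male vs. female), and SBP", with SBP split at 120–139 and 140–159 mmHg. Under Casual Systolic Blood Pressure, baseline SBP is the average of two measurement days.

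**The concern.** The design collects baseline SBP carefully and balances the arms on age, sex and SBP, but the powered test draws on this only by subtracting baseline. That has two consequences.

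- **Slope fixed at 1.** A change score is the most precise use of baseline only if follow-up SBP rises one for one with baseline SBP. In a group selected for raised SBP the slope is likely to be below 1, because of regression to the mean. Any baseline imbalance left after stratification then adds noise to the effect estimate.
- **Strata ignored.** Stratified randomisation removes part of the between-arm variation. A t-test that does not condition on the strata still counts that variation in its standard error, so the error is overstated.

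The regression would recover most of this, but it is presented as an addition to the t-test, its list is illustrative, and sex is not named. At stake is some precision on the primary question, and clarity about which result answers it.

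**Working it through.** **1. Reproduce the plan's figure.** Inputs from Statistical Design, Power, and Analysis Plan: difference 8.6 mmHg; SD of change 11.6 and 13.5 mmHg; two-sided α = 0.05; power 90%; dropout 20%.

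- Pooled SD = √((11.6² + 13.5²)/2) = 12.59; d = 8.6/12.59 = 0.683 (stated 0.68).
- Noncentral t with d = 0.68 gives 46.4 per group, so 47; power at 47 is 90.4%.
- 94/0.8 = 117.5, so 118.

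The stated 47, 94 and 118 all reproduce for the t-test on change. Its standard error is 12.59 × √(2/47) = 2.60 mmHg and its 95% CI half-width is 1.986 × 2.60 = 5.16 mmHg.

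**2. Gain from adjustment, equal SDs at both times (assumption).** Var(change) = 2σ²(1 − ρ), and the ANCOVA residual variance is σ²(1 − ρ²). The ratio is (1 + ρ)/2. The document does not give ρ, so a range is shown with the SD of change held at 12.59 and 47 per group. Power uses the unrounded d = 0.683, which is 90.6% without adjustment.

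| Assumed ρ | Variance ratio | CI half-width (mmHg) | CI narrower by | Power | Implied SD of SBP (mmHg) |
|---|---|---|---|---|---|
| 0.4 | 0.70 | 4.31 | 16% | 97.5% | 11.5 |
| 0.5 | 0.75 | 4.47 | 13% | 96.6% | 12.6 |
| 0.6 | 0.80 | 4.61 | 11% | 95.6% | 14.1 |
| 0.7 | 0.85 | 4.75 | 8% | 94.5% | 16.2 |
| 0.8 | 0.90 | 4.89 | 5% | 93.3% | 19.9 |

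The last column is 12.59/√(2(1 − ρ)). For comparison, eligibility spans 120–159 mmHg. A uniform spread over 39 mmHg has SD 39/√12 = 11.3, and the largest possible SD is 39/2 = 19.5. Baseline readings taken after screening can fall somewhat outside this range.

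**3. Gain with a smaller baseline SD.** Assume a baseline SD of 10 and the same SD of change (variance 158.4). Solve 10² + s² − 2ρ·10·s = 158.4 for the follow-up SD s. The variance ratio is then s²(1 − ρ²)/158.4.

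| Assumed ρ | s (mmHg) | Variance ratio | CI narrower by |
|---|---|---|---|
| 0.3 | 11.2 | 0.72 | 15% |
| 0.5 | 14.1 | 0.946 | 2.8% |
| 0.7 | 17.4 | 0.971 | 1.5% |

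**4. Effect of ignoring the strata.** Simulation under no treatment effect: 94 participants, eight strata, blocks of 4 (assumed), SBP with SD 14 before truncation to 120–159, small age and sex effects, 1,500 runs per row.

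| Assumed r | t-test: mean model SE | t-test: empirical SE | Excess | t-test type I error | With baseline: model / empirical SE | With baseline: type I error |
|---|---|---|---|---|---|---|
| 0.4 | 2.92 | 2.68 | 9% | 3.3% | 2.65 / 2.61 | 4.6% |
| 0.6 | 2.45 | 2.34 | 5% | 4.0% | 2.32 / 2.29 | 5.1% |
| 0.8 | 1.79 | 1.74 | 2.5% | 4.3% | 1.74 / 1.73 | 5.0% |

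Adding age and sex to baseline changed little. A separate illustrative simulation, also with eight strata and blocks of 4 (4,000 runs, its own assumed SDs), gave a t-test model SE of 2.31 against an empirical 2.19–2.24, an excess of 3–5%, with type I error 4.2%. ANCOVA there had an SE of 2.10, so the variance of the estimate fell by 1 − (2.10/2.24)² = 12% or 1 − (2.10/2.19)² = 8%.

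**The case against.** The strongest reply is that nothing is broken. The t-test keeps its type I error at or below 5%, the trial has its planned 90% power under its own assumptions, and the regression already names baseline BP and age, which are two of the three stratification variables. The phrase introducing the covariates does not exclude sex, and a condensed article may leave the final list to the analysis plan. All of this stands. It makes the point an improvement in efficiency and clarity, not a fault in validity.

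A reader might infer more than the document supports:

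- **That baseline SBP is ignored.** It is not. A change score subtracts it, and the regression adjusts for it.
- **That adjustment would cut variance by 15–35% and lift power to 94–98%.** Those figures follow from ρ = 0.7 to 0.3 with equal SDs. Neither is documented, and the formula takes no account of the SBP stratification, which already removes part of the baseline imbalance. The simulated empirical SEs of 2.19–2.24 against 2.10 imply only 8–12%.
- **That false positives are more likely.** The t-test errs in the conservative direction, and its place as the powered test, with regression added afterwards, points to it as the deciding analysis.
- **That adjusting for antihypertensive use conditions on a consequence of treatment.** Informed Consent and Screening and Baseline Assessments both ask for a stable regimen throughout, so this is minor, as is the word used for the covariates.

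One part of the objection is weaker than it looks. It is true that the gain is small if ρ is high, but with equal SDs ρ = 0.8 implies an SBP SD of 19.9 mmHg, beyond what the eligibility range allows. The larger gains are therefore not implausible, though the small-gain case in step 3 also fits the stated SD of change.

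**Conclusion.** The point holds as a nearly free improvement. The powered comparison is valid but somewhat inefficient, and its standard error is about 3–9% too large in the simulations, under assumed block size, SBP distribution and correlation. Adjustment would narrow the confidence interval by about 5–16% for ρ = 0.8 to 0.4 with equal SDs, and by as little as 1–3% with a baseline SD of about 10 mmHg and ρ of 0.5 to 0.7. The document does not give the inputs needed to place the trial within that span. The sample size needs no change.

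**What to change.** State one primary analysis: an ANCOVA of end-of-treatment casual SBP on treatment, continuous baseline casual SBP, age, sex and the SBP randomisation stratum. Use the same form for 24-h SBP and CFPWV, each with its own baseline value. Close the covariate list. If antihypertensive medication is included, define it as use at baseline. Keep the change-score t-test as a supportive analysis.

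Cost: a sentence or two in the analysis plan, and about 4 of the 92 residual degrees of freedom (94 − 2). No new data and no change in sample size are needed.

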### Other Outcomes

#### Safety and Tolerability

All subjects will report to the laboratory every 2 weeks during the 3-month treatment period (Visits 5–9, Figure 2) to meet with a study nurse. Safety, i.e., risk to the subject, will be assessed by recording the number and severity of adverse events. Tolerability, i.e., the degree to which overt adverse events are tolerated by participants, will be determined based on the number of participants that drop out of the study due to adverse events.

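### Tolerability is counted only by leaving the study, so stopping pills for an adverse event while staying in is missed; the t-test sentence also needs limiting to continuous outcomes with a baseline

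*Protocol article*

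**What the plan says.** Under Other Outcomes, the Safety and Tolerability section gives two measures. For the first: "Safety, i.e., risk to the subject, will be assessed by recording the number and severity of adverse events". Tolerability is described as how far overt adverse events are tolerated, and is "determined based on the number of participants that drop out of the study due to adverse events". Adherence is a separate outcome: the percentage of prescribed pills taken, from pill counts at the fortnightly visits.

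The Statistical Design, Power, and Analysis Plan section says that the t-test will be used "to compare the change in outcome measures between nicotinamide riboside and placebo treatment groups", and gives the reason: "because all outcome variables are continuous". It continues: "All outcome variables will be assessed and confirmed for normality and data transformations will be performed, if necessary, prior to performing comparisons". It then commits all comparisons to the intention-to-treat principle at two-sided α = 0.05. Just before the t-test sentence, the same section says "Descriptive statistics will be provided for all baseline and outcome variables" and that "proportions will be calculated for categorical or ordinal variables", with 95% confidence intervals where appropriate.

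**The concern.** There are two linked problems.

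**The tolerability measure does not match its own concept.** Leaving the study and stopping the product are different events. The measure records only the first, while the stated concept, whether adverse events are tolerated, is closer to the second. An intention-to-treat comparison depends on testing people after they stop treatment, so good conduct of the trial moves people out of the tolerability count. The Discussion says the trial will determine whether the product is tolerable, and this measure can make that answer look better than it is.

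**The reason given for the t-test is false as written.** The article's own outcome list includes a count, a severity grade and a yes/no event. None has a pre-treatment value, so none has a change score. Percentage of pills taken is numerical but also has no baseline. A normality check or a transformation has no meaning for a yes/no outcome.

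**Working it through.** **1. What the tolerability measure counts.** In one arm, let *d* be the number who leave the study because of an adverse event, and *s* the number who stop the pills permanently because of an adverse event but stay for testing.

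- Count under the stated definition: *d*
- Participants who stopped the product for an adverse event: *d* + *s*
- Share missed: *s* / (*d* + *s*)

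If nobody who stops stays (*s* = 0), nothing is missed. If everybody who stops stays (*d* = 0), everything is missed and the reported figure is zero. The document gives neither number, so the share can lie anywhere from 0 to 100%. The pilot's 20% drop-out rate does not help, because it is not broken down by reason.

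**2. Whether the data exist to correct it.** The Adherence section has pills counted at each fortnightly visit. The Intervention section has symptoms reported and unused pills returned at the same visits. The Study Withdrawal section covers only withdrawal of consent and removal from the study; it does not mention stopping pills while staying in. Stopped pills would therefore appear as low adherence, but not as a tolerability event. The one item not stated to be recorded is the reason for stopping.

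**3. Outcomes set against the t-test sentence.**

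| Outcome | Type | Baseline value? | Change score? |
|---|---|---|---|
| Casual SBP, 24-h SBP, CFPWV | continuous | yes | yes |
| NAD+ metabolites, blood biomarkers | continuous | yes | yes |
| Adverse events: number, severity | count, ordinal | no | no |
| Drop-out for adverse events | yes/no | no | no |
| Percentage of pills taken | numerical, 0–100 | no | no |

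The sentence fits the first two rows and fails for the other three.

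**4. Whether the primary design is touched.** Pooled SD = √((11.6² + 13.5²)/2) = 12.59; effect size = 8.6/12.59 = 0.683 (stated 0.68). With the noncentral t distribution, d = 0.68, two-sided α = 0.05 and 90% power require 46.4, so 47 per group, and power at 47 is 0.904. Enrolment is 94/0.8 = 117.5, so 118, or 59 per group. All the stated figures reproduce, and none depends on the safety outcomes.

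**5. Whether a t-test on a yes/no outcome would mislead.** The check used 59 per arm and assumed the same rate of drop-out for adverse events in both arms, from 1% to 20% (the document gives no rate). All pairs of binomial counts were enumerated and the probability of p < 0.05 summed:

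| Assumed rate | t-test | Fisher's exact |
|---|---|---|
| 1% | 0.003 | 0.00003 |
| 2% | 0.019 | 0.0007 |
| 3% | 0.035 | 0.003 |
| 5% | 0.046 | 0.010 |
| 10% | 0.050 | 0.021 |
| 20% | 0.049 | 0.028 |

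Single tables at 59 per arm give these p-values:

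| Events | t-test | Fisher | Barnard | Boschloo |
|---|---|---|---|---|
| 0 vs 5 | 0.022 | 0.057 | 0.023 | 0.038 |
| 1 vs 7 | 0.028 | 0.061 | 0.034 | 0.041 |

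The t-test is conservative when events are sparse and does not materially exceed 0.05 in this range. Fisher's test stands apart because it is the more conservative, while two unconditional exact tests fall below 0.05 in both tables, as the t-test does.

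**The case against.** Four things can be said on the other side.

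- **The t-test is not assigned to safety.** This stands. No sentence names it for adverse events or drop-outs, and since these have no change score, the natural reading is that the sentence covers outcomes measured before and after treatment. A reader might infer that the plan prescribes an invalid test for safety; the document does not say so.
- **Non-continuous outcomes already have a route.** This stands in large part. Proportions and, where appropriate, 95% confidence intervals are provided in the same section. The choice of interval and the safety population are details that a condensed article may leave to the full plan, and their absence is not a fault here.
- **There is no statistical harm.** This stands. A reader might infer that a t-test on sparse yes/no data gives p-values that are too small, and that Fisher's test is needed. The enumeration does not support either inference.
- **The tolerability measure is explicit, and pill counts catch those who stop.** This stands only in part. The definition is clear, but it counts the wrong event for its stated concept. Pill counts show that pills were not taken; they do not record an adverse event as the reason, and they feed a different outcome.

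A reader might also treat the matter as central because the design section names safety beside efficacy. The Abstract and outcome sections, however, place safety, tolerability and adherence under other outcomes, below the primary and secondary ones.

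**Conclusion.** The point holds as a minor one. As defined, the tolerability measure misses anyone who stops the pills for an adverse event and stays in the study. The size of the undercount cannot be given from the document. The conclusion assumes that some who stop pills are retained for testing, which the intention-to-treat commitment implies but no passage spells out.

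The statement that every outcome is continuous is untrue for adverse events and for drop-out due to them, and a change score does not exist for these or for adherence. This part is close to a correction of wording. Casual SBP, 24-h SBP and CFPWV are continuous with baseline values, so the t-test on change suits them and the sample size stands.

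**What to change.** **Safety and Tolerability section.** Define tolerability as permanent discontinuation of study pills due to an adverse event, whether or not the participant stays in the study. Report study drop-out for adverse events beside it.

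**Analysis section.** Limit the t-test on change, and the normality check and transformation, to continuous outcomes with a baseline value, and remove the statement that every outcome is continuous. Report adverse events, pill discontinuations and drop-outs for adverse events by arm as counts or proportions, with risk differences and 95% confidence intervals. Compare percentage adherence between arms directly, not as a change.

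**Cost.** A few lines of text. Nearly all the data already come from the fortnightly symptom reports and pill returns; the addition is to record the reason when a participant stops the pills. The tolerability figure may turn out less favourable than one based on study drop-out alone.

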### Primary Outcome

#### Casual Systolic Blood Pressure

Casual (resting) SBP and DBP will be measured and classified according to 2017 American College of Cardiology/American Heart Association guidelines (3). Subjects will rest quietly in the seated position for at least 5 min with their back supported, feet flat on the floor, and arm at heart level. BP will be measured in triplicate, with a 2-min recovery between each measure, over the brachial artery of the non-dominant arm *via* automated oscillometric sphygmomanometer (Mindray), validated according to the Association for the Advancement of Medical Instrumentation standards and regularly calibrated by the manufacturer (28). Casual SBP, DBP, and pulse pressure will be defined as the average of the 3 measurements. Casual BP will be measured on 2 separate days at least 24 h apart both at baseline and at the end of the 3-month treatment period (Figure 2) and averaged over the 2 measurement days. Casual BP also will be measured every 2 weeks during the supplementation period.

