### Selection and Treatment of Subjects

#### Study Location and Timeline

All study visits will be performed at the Clinical Translational Research Center (CTRC) at the University of Colorado (CU) Boulder Campus. To account for an approximate 20% dropout rate, we plan to enroll 118 subjects to achieve our goal of completing testing on 94 participants.

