#### Study Withdrawal

Participants can withdraw their informed consent at any time and for any reason. Investigators may also remove participants from the study at any time due to significant non-compliance with the protocol (i.e., procedures, assessments); any adverse event that, in the opinion of the medical director, indicates that continuing in the study is not in the best interest of the participant; loss of the participant’s ability to freely provide consent; or other serious changes in physical or mental health.

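### The article claims intention to treat, but its named test needs a 3-month value and no 3-month measurement is provided for participants who stop, so the likely primary comparison covers about 94 of 118 randomised

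*Protocol article*

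**What the plan says.** Under Statistical Design, Power, and Analysis Plan the article declares "All comparisons will be made on intention to treat principle", and that "conclusions will be made using a two-sided significance level of α = 0.05". The primary comparison is a t-test on change between the two groups, with linear regression to adjust for factors such as age, baseline BP and antihypertensive use. The Outcomes section places outcome measurement at baseline and after the 3-month supplementation period.

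The same statistical section sizes the trial at 47 per group for 90% power and then allows for 20% dropout: "a total of 118 participants will be enrolled and equally randomized to an intervention group, with 59 participants/group". Study Location and Timeline puts the aim in terms of completion: "we plan to enroll 118 subjects to achieve our goal of completing testing on 94 participants".

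Three further sections bear on who has a 3-month value:

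- Post-intervention Assessments describes Visits 10 and 11 for participants who have finished 3 months of treatment, and has them continue their pills through post-testing.
- Study Withdrawal says "Investigators may also remove participants from the study at any time due to significant non-compliance with the protocol", where compliance is explained as procedures and assessments. It also lists adverse events, loss of the ability to consent, and serious changes in health.
- Casual Systolic Blood Pressure adds that "Casual BP also will be measured every 2 weeks during the supplementation period". No analytic use of these readings is stated.

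**The concern.** An intention-to-treat comparison needs two things: everyone counted in the arm to which they were randomised, and an outcome, or a stated way of handling its absence, for each of them. The article declares the principle, but the conduct it describes does not supply the outcomes. A t-test on change, or a regression on the same change, has nothing to work with for a participant who left before Visits 10 and 11.

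This matters because leaving may not be independent of treatment. Safety and Tolerability measures tolerability by the number who drop out because of adverse events, so the article itself treats that kind of dropout as something the intervention may influence. If the reasons for leaving differ between arms, a comparison of those who remain is no longer protected by randomisation, and a result labelled intention to treat could rest on a selected four-fifths of those randomised. A 3-month reading that was never taken cannot be recovered at the analysis stage.

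**Working it through.** **1. Reproduce the stated sample size.** Inputs from Statistical Design, Power, and Analysis Plan: difference in change 8.6 mmHg; SDs of change 11.6 and 13.5 mmHg; two-sided α = 0.05; power 90%.

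- Pooled SD = √[(11.6² + 13.5²)/2] = 12.59 mmHg.
- Standardised effect = 8.6/12.59 = 0.683; the article gives 0.68.
- The t-based solution at 0.68 is 46.4 per group, rounded up to 47. Power at 47 per group is 90.4%.
- Dropout allowance: 94/0.8 = 117.5, rounded up to 118, or 59 per group.

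All the stated figures reproduce. There is no arithmetic error.

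**2. Share of those randomised who would enter the named test.** Expected with a 3-month value: 94/118 = 79.7% (47/59 per arm). Expected without one: 118 − 94 = 24, or 20.3%.

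**3. Set the sections side by side.**

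| Section | What it fixes |
|---|---|
| Statistical Design, Power, and Analysis Plan | Intention to treat; t-test on change |
| Outcomes | Outcome defined at baseline and 3 months |
| Post-intervention Assessments | Post-testing described for those who finish treatment |
| Study Withdrawal | Removal is from the study; later measurement not mentioned |
| Study Location and Timeline | 94 of 118 expected to complete testing |

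No section provides Visits 10 and 11 for someone who stops. Followed as printed, the sections lead to the 79.7% in step 2.

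**4. What the 90% power refers to.** It is the power of a comparison of 47 per arm with the full 8.6 mmHg effect. The document does not say what effect people who stop would show, so the following is an assumption with its full range. Suppose all 59 per arm are measured, 20% stop, the SD stays at 12.59, and those who stop keep a fraction r of the effect. The effect in all randomised is 8.6 × (0.8 + 0.2r).

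| r | Effect (mmHg) | Effect/SD | Power, 59 per arm |
|---|---|---|---|
| 0 | 8.6 × 0.8 = 6.88 | 0.547 | about 84% |
| 0.5 | 8.6 × 0.9 = 7.74 | 0.615 | about 91% |
| 1 | 8.6 × 1.0 = 8.60 | 0.683 | about 96% |

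At r = 0, about 72 per arm (71.3 rounded up) would be needed for 90%.

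**The case against.** The strongest objection is that the document nowhere says participants without a 3-month value will be left out. It defines no completer or per-protocol set, and it does not say that data from removed participants are discarded. How missing outcomes enter the analysis is commonly left to a statistical analysis plan, and none is shown. That stands as far as the missing-data method goes: a completer analysis is the likely default, not a stated plan. It does not settle whether people who stop are still measured at Visits 10 and 11. That is trial conduct, and no analysis plan can supply readings that were not taken.

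Several stronger readings are tempting, and the document does not support them:

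- *That sizing on 94 and inflating to 118 contradicts intention to treat.* Dividing an evaluable number by one minus the dropout rate is standard practice, and the 94 is a recruitment goal, not an analysis set.
- *That poor pill-takers, or people whose BP rises, will be removed.* The withdrawal text explains non-compliance as procedures and assessments. Pill count is a separate outcome under Adherence, and rising BP is not listed. The clause is also permissive.
- *That the resulting bias favours nicotinamide riboside.* Only an overall 20% dropout is given, with no figure by arm. If people left because BP rose and the product worked, more would leave placebo, which would shrink the difference.
- *That the result would be overstated by 1.7 mmHg.* This is 8.6 − 6.88, and it rests wholly on assuming no effect in those who stop.

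Not using the two-weekly readings can also be defended. The Outcomes section says check-ins are made without restrictions, whereas the endpoint is a two-day average under controlled conditions. This calls for care in modelling but does not make the readings uninformative.

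**Conclusion.** The point holds as a mismatch between the declared principle and the conduct and test printed beside it. Following the text gives a likely primary comparison of about 94 of 118 randomised (79.7%), given the article's own 20% dropout and no rule for missing 3-month values. Missingness may be related to treatment; the direction and size of any bias cannot be derived from the document.

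The sample size is correct. The qualification is that the 90% describes about 94 people with 3-month data and the full effect. For an analysis of all 59 per arm, power ranges from about 84% to about 96% across the assumed range from no effect to full effect in those who stop. The planned number may therefore be slightly short or more than enough.

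The point deserves action because it touches the primary result and the lost measurements cannot be recovered later.

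**What to change.** 1. **Follow-up.** Reconcile Post-intervention Assessments, Study Withdrawal and the statistical section by separating the end of study treatment from the end of outcome follow-up. State that randomised participants who stop are still invited to the Visit 10 and 11 BP measurements where consent and the medical director's judgement allow. The clinical grounds for removal stay as they are.
2. **Primary analysis.** Analyse everyone randomised, as assigned, with a likelihood-based repeated-measures model or multiple imputation. Use baseline, two-weekly and 3-month casual SBP, fit visit-specific means because check-ins are unrestricted, and take the treatment contrast at 3 months.
3. **Labelling.** Call the t-test in those with 3-month data supportive, and state that the 90% power applies to that set. If power for all randomised is also quoted, give it with its assumption about those who stop.

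The cost is a short amendment to the withdrawal and analysis wording and some post-test visits for people who stopped. The check-in BP readings are already collected. The expected effect in all randomised may be smaller than 8.6 mmHg.
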